### Study 2: Development and Validation of an American Indian Mammography Services (AIMS) Survey

The majority of mammography patient satisfaction studies have been conducted using assessment instruments whose psychometric properties were not tested, have been tested outside of the United States, or have not focused on the at-risk American Indian/Alaskan Native population. In this study, we will develop and validate a mammography patient satisfaction instrument that will be tailored for use by American Indian/Alaskan Native women. To develop a culturally appropriate patient satisfaction assessment we will identify the mammography experiences and issues that affect the satisfaction of American Indian women through the information gleaned from the focus groups performed with AI/AN women for this study as well as [name] prior focus groups with Non-Hispanic White, Hispanic, and Black women.

#### Development of an American Indian Mammography Satisfaction (AIMS) Survey

A mammography patient satisfaction survey was developed originally in 1991 by Cockburn and her colleagues [73]. This instrument includes 6 subscales: 1) convenience and accessibility, 2) staffs' interpersonal skills, 3) information transfer, 4) physical surroundings, 5) perceived technical competence of staff, and 6) general satisfaction. The reliability and validity of this instrument has been tested through research conducted in Australia. [name] mammography workgroup has also developed the Patient Assessment of Mammography Services (PAMS) mammography satisfaction for use with the general U.S. population. The PAMS survey assessed mammography satisfaction in the following areas: appointment scheduling, facility environment, exam, mammography technologist, mammography results reporting, and overall satisfaction. An additional open-ended question asked women to provide suggestions for improving the mammography experience. The Cockburn et al. and PAMS instruments will serve as the basis for our culturally tailored American Indian Mammography Satisfaction (AIMS) survey. We intend to modify and supplement these instruments by including questions that relate to the main themes and ideas generated through the focus groups that are not included in the Cockburn instrument. We will categorize questions into subscales and anticipate that additional subscales, beyond those included in the Cockburn instrument and our research team's PAMS survey, will include greater detail on facility access, hours of operation, acceptance of self-referrals, ease of making an appointment, location/type of facility, the use of reminder postcards or calls to patients, or the mode and timeliness of reporting exam results to patients. We will calculate patient satisfaction scores by numerically assigning each possible answer and summing answers within each scale. A global satisfaction score will be obtained by summing all subscale scores. We will also collect demographic data on participants' date of birth, education, marital status, income, employment status, race/ethnicity (e.g., American Indian, Alaskan Native, or mixed race), the number of mammograms obtained in the past, and history of breast malignancies. Our goal is to develop a brief instrument that can be administered easily.

##### Internet-Based Health Information

More health consumers are using the Internet for information than ever before, including lower-income, less educated, and minority Americans [81]. Studies show health-seeking Internet use among low-income AA [82], low-income AA parents [83], White parents [84], AI [85], and Latinos [86]. However, there is a persistent gap in computer and Internet use between the majority population and ethnic minorities, low-income, and rural populations, though there are large increases in computer ownership and Internet use over time among all demographic groups [87]. Overall, Whites are more likely to use the Internet than Latinos and Latinos are more likely to use the Internet than AA [88]. AI have not been compared to other ethnic groups [85]. Patients are likely to share the information they learn online with providers, find the information useful, and make changes based on it [82-84,89]. Therefore, information must be accurate and appropriate for the people using it, in terms of culture, literacy, and ease of use or navigation [81,87,90-93]. Trends in the digital divide may be changing, as the gap between the majority population and others is decreasing and there has been a significant increase in the public availability of computers and Internet access at schools, public libraries, and workplaces [94]. Our own studies among AI show a strong interest in using the Internet for health information, an acceptance of using computers in public places, and a preference for culturally-tailored applications and information. In her prior studies with the American Indian population, [name] has found success with the use of Internet-based surveys. As such, the AIMS will be designed as an instrument that is completed by participants via the Internet (a corresponding paper survey will also be available for those with a preference for paper-based surveys).

#### Internet-Based AIMS Survey (Programming and Development)

##### Comprehensive Research Information System (CRIS)

The Internet-based AIMS survey will be made available through a state-of-the-art Clinical Information Management Database System that supports a Comprehensive Research Information System (CRIS). The database system is a secure, 21 CFR Part 11-compliant, robust and scalable system such that data can be entered efficiently and in a standardized format. This web-based system allows for direct data entry from participants. Among other things, the comprehensive database management system supports participant recruitment, study monitoring, data safety monitoring, and query management.

Our Comprehensive Research Information System provides capabilities to: 1) create, maintain, and edit participant data; 2) track study protocol versions, amendments, and IRB approvals/renewals; 3) create participant screening and enrolling criteria; 4) create and disseminate case report forms for outcomes studies; 5) create participant schedules and record participant status; 6) create user and multi-organization research networks; 7) record, maintain, and report adverse events; 8) conduct study queries and generate standard and ad hoc reports; and 9) export clinical data to third party analytical tools, such as SAS and Microsoft Excel. In addition, the system will allow for real-time monitoring of participant survey completion and patient data with built-in data quality, auditing, and integrity checks. The system will provide our researchers with a central repository for all study related documents and also will allow for the automation of research administration activities.

##### Healthy Living American Indian Women Internet Portal

The Healthy Living American Indian Women Internet portal will be developed as a separate website from the actual CRIS database. The Healthy Living American Indian Women Internet portal website will be linked with the CRIS database so that any survey completed within the Healthy Living American Indian Women Internet portal is transmitted back to the CRIS database and resides there under that specific participant information. This is how we will protect the integrity and security of the data collected. The AIMS survey participants will not have access to the actual CRIS database and they cannot alter the AIMS survey housed on the Healthy Living American Indian Women Internet portal website, they can only fill it out and submit it.

##### Survey Form Development

Through previous collaborations with various clinical research groups, the Center for Biostatistics and Advanced Informatics (CBAI) staff has over 40 years collective experience in the design, development, validation and implementation of survey forms that are consistent with protocol, reporting and various sponsor requirements. The design of the AIMS survey will be collaboration between the Clinical Information Specialists of the CBAI, the project director ([name]), the Principle Investigator ([name]), and the study statistician ([name]). Once all variables of interest have been identified and verified with the study endpoints and proposed analysis, the initial drafts of the AIMS survey will be designed in the development environment of the comprehensive research information system. Once the AIMS survey is created, it will be reviewed for completeness, accuracy and utilization by study staff and expert reviewers. Mock AIMS surveys as well as AIMS pilot testing will be completed to ensure compatibility with the data being collected in the source documentation as well as used for validation of the range, logic and other edit checks in the web-based data entry system. Once the AIMS survey is validated and final, it will be locked to format and editing in the system and added to the production environment for remote data entry.

Women who express interest in participating in the study will be assigned a unique identifier upon their first visit to the site. This ID will allow participants to save their AIMS survey in progress and return later for completion. Each participant will be provided with directions for the location of the AIMS web-survey: once she is at the website, the participant will have to enter her unique ID and a password to access the AIMS survey.

##### Web-Survey Technical Difficulties

Using a web application will ensure that all interested women will be able to access the AIMS survey. While most women will likely participate using laptop computers made available by the research team at recruitment events, a number of others will be more comfortable with accessing and completing the AIMS survey in the privacy of their own home. The minimum requirements will be a computer running an Internet Explorer version 4.0+ or equivalent and access to the internet. This includes more than 99% of all computers (browser usage from http://www.thecounter.com/stats/). Women who forget or lose their unique ID and password will be addressed by having users identify and answer "secret" questions upon their first visit to the site (e.g., First pet's name?). This information will be stored separate from study data. A participant who forgets her ID will be able to retrieve it by answering the questions she identified and answered.

##### AIMS Content Validity

We will use American Educational Research Association, American Psychological Association, and National Council on Measurement in Education's *Standards for Educational and Psychological Testing *released in 1999 to guide our instrument validation process. Goodwin provides a summary of these validation standards [95]. During our AIMS pilot testing phase, we will first garner evidence for instrument content. A panel of nine content experts from the fields of breast screening, cancer control, and American Indian health will evaluate the items and instrument according to the procedure set forth by Grant & Davis [96]. They will receive a content review form divided into domains, each with an accompanying definition, and will be asked to rate the items' relevance to the domain on a 4-point scale, (i.e. from 'not relevant' to 'highly relevant'). We will drop, revised, or kept items based on responses across experts, using the item content validity index [97]. The instrument will undergo a final review for readability and design by the project investigators. Additionally, we will use content information to re-calculate sample sizes for participant portion of this study if necessary.

#### AIMS Pilot Test

We will conduct mock tests of the AIMS Internet instrument and analyze the questions for logistical problems such as skip patterns, range errors, and response issues. Once all logistical issues are resolved, we will pilot the AIMS Internet survey with a sample of 50 American Indian/Alaskan Native women. The pilot testing procedure described below will allow us to administer the AIMS to a sample of women to determine if the questions are presented in a clear and understandable manner, assess the face validity of the questions, and evaluate the survey administration procedure. The pilot test will help guide the final refinement of the AIMS.

After completing the AIMS web survey, additional questions will be tagged on the end of the assessment that inquire about: 1) whether participants felt the survey questions clearly assessed the important aspects of mammography services, mammography satisfaction and dissatisfaction, and barriers to mammography utilization, 2) whether participants felt comfortable responding to all of the questions, 3) perceptions regarding the clarity and completeness of the information included in the AIMS survey, 4) the personal relevancy of the survey topics, and 5) the readability/presentation of the AIMS survey. Survey items will be revised based on feedback and re-piloted with additional participants until an acceptable AIMS survey has been developed.

##### AIMS Pilot Testing Recruitment

AIMS pilot testing participants will be recruited at the Haskell Health Center through referral from clinic personnel and through posters in the waiting area. Participant eligibility criteria are outlined in Table 3.

**Table 3 T3:** Participant Eligibility

Inclusion Criteria	Exclusion Criteria
• Aged ≥40 years of age • Mammogram within past 5 years • Last mammogram at IHS or non-IHS facility • Home address & access to a working telephone • American Indian/Alaskan Native • Female	• Cognitive impairment • Another household member enrolled in the study • High risk for breast cancer

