Using their validated patient satisfaction questionnaire, Cockburn et al conducted a study to evaluate differences in satisfaction between persons attending an Australian screening facility for initial screening (N = 481) and recalls for additional views (N = 318) [71]. High satisfaction was found on most subscales among those attending the screening clinic while slightly lower satisfaction levels were reported in staff interpersonal skills, information giving, physical surroundings, convenience and accessibility, and general satisfaction subscales by those attending the recall clinic. Delays in reporting of results, however, were the source of most dissatisfaction among the recall clinic attendees.

Decker et al. [72] used a questionnaire developed by Cockburn [73] to examine differences in patient satisfaction by screening location and screening result following mammography. The setting included two screening facilities in Canada. The results of the study indicate overall high levels of satisfaction. Significant differences were found between the sites with respect to convenience and accessibility of the facilities and information transfer. In addition, women with abnormal findings were more likely to be dissatisfied with their mammography experience. This is a particularly important finding given that women with an abnormal result may be at increased risk for breast cancer. One drawback of this study was that 16% of the study sample (N = 1,176) completed the satisfaction question more than 12 months after their last mammography appointment at the facility, thereby introducing a recall bias.

An adapted version of Cockburn's instrument was also used in a study of 109 women who obtained mammograms at one of six different facilities. Dullum et al. determined that factors significantly associated with discomfort during mammography include patient perceptions of a technologist's "roughness" and the facility that a woman attended [74]. This study is also one of the largest comparisons of patient satisfaction among mammography facilities. In this study, however, it is unclear to what the facility-based differences may be attributed. For example, the differences may be due to technologist characteristics, differences in facility ambience, or issues related to patient access to the facility.

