##### Participants

Twelve focus groups, each comprised of 8-12 unacquainted individuals, will be conducted. Focus groups will be conducted with American Indian/Alaskan Native women and will be stratified by residential location of participants (e.g., rural or reservation vs. urban). Participants will include women who are 40 years of age and older (in concordance with the American Cancer Society's recommended beginning age for annual screening of asymptomatic women) and will be further stratified by age (e.g., 40-64 year-olds and those aged 65 years and older). All participants will have had at least one mammogram performed within the past five years.

Focus group participants will be recruited at an Indian Health Service clinic through referral from clinic personnel and through posters in the waiting area. Participants who do not use the above-mentioned health service clinic may be more difficult to reach because there is no central location through which to reach them. We will post flyers and posters at various community locations in the four primary Kansas Indian Reservation sites located in Horton (Kickapoo), White Cloud (Iowa Tribe of Kansas and Nebraska), Mayetta (Prairie Band Potawatomi Nation), and Reserve (Sac and Fox Nation) Kansas. We will also post flyers at other local AI/AN venues including the Heart of America Indian Center and the offices of the American Indian Council. A brief questionnaire at the time of recruitment will allow us to assign groups based on the sampling frame illustrated in Table 2.

**Table 2 T2:** Focus Group Sampling Frame

AI/AN Women			
**Age 40-64**		**Age 65+**	

**Rural/Reservation**	**Urban**	**Rural/Reservation**	**Urban**

3 groups	3 groups	3 groups	3 groups

36 participants	36 participants	36 participants	36 participants

Focus group moderator's guides will be developed with input from program advisory board members and will be based partially on information from our prior mammography focus groups with Non-Hispanic White, Hispanic, and Black women. Discussions will focus on barriers to obtaining mammograms, motivating factors to obtain mammograms, past mammography experiences, and areas of mammography satisfaction and dissatisfaction.

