##### Mammography Satisfaction Variation

We will use descriptive statistics to explore the extent to which the mammography experiences and mammography satisfaction of American Indian/Alaskan Native women vary. Frequencies and percentages will be used to summarize categorical demographic information of the participants surveyed. The primary outcome will be the global satisfaction score on the AIMS with secondary outcomes being the derived AIMS subscales. AIMS subscales will be derived from barriers cited by focus group participants and confirmed through factor analytic procedures conducted during the AIMS pilot test. Projected subscales will include service accessibility, results reporting procedures, staff interpersonal skills, perceived technical competence of staff, and global satisfaction. To model the global AIMS scores on individuals adjusting for individual factors (age, race/ethnicity, etc.), linear regression models will be developed. Similar models will be developed for AIMS subscale scores.

Using global patient satisfaction as the primary outcome variable, we also then conduct comparison of AIMS survey characteristics between women who sought services within and outside of the Indian Health Service system. This will be done by averaging the global AIMS scores for participants with an Indian Health Service-sponsored mammogram and those with a non-Indian Health Service-sponsored mammogram. Similar averaging will be done for each AIMS subscale to obtain global AIMS subscale scores.

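### Women may rate a mammogram up to five years old, although the protocol faults an earlier study for recall beyond 12 months; the date of the rated mammogram is not listed as collected, and no stated analysis uses it.

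*Protocol article*

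**What the plan says.** - **Eligibility.** Table 3 (AIMS Pilot Testing Recruitment) lists "Mammogram within past 5 years" as an inclusion criterion. The focus groups use the same window: "All participants will have had at least one mammogram performed within the past five years" (Study 1, Participants).
- **The protocol's own view of recall.** In the section Satisfaction with Mammography, a Canadian study is faulted because 16% of its sample "completed the satisfaction question more than 12 months after their last mammography appointment at the facility, thereby introducing a recall bias".
- **Data collected.** The section on development of the AIMS survey lists "date of birth, education, marital status, income, employment status, race/ethnicity" and then "the number of mammograms obtained in the past, and history of breast malignancies". Neither the date of the rated mammogram nor the time since it is in the list.
- **Analysis.** Under Mammography Satisfaction Variation, the global score is modelled "adjusting for individual factors (age, race/ethnicity, etc.), linear regression models will be developed". The IHS contrast is described separately: "This will be done by averaging the global AIMS scores for participants with an Indian Health Service-sponsored mammogram and those with a non-Indian Health Service-sponsored". Time since mammogram is not mentioned as a covariate, stratum, restriction or sensitivity analysis.

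**The concern.** The protocol sets a benchmark when it criticises other work, then admits recall up to five times as long (60 against 12 months) without comment. A wide window can be defended in a population with low screening rates. The weakness is that nothing in the plan lets the analyst see or control what the window brings in.

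The main exposure is Aim 3, the comparison of global satisfaction between women with IHS and non-IHS mammograms. If time since the visit differs between these groups and ratings drift with time, the difference in means mixes quality of service with length of recall. A larger sample does not remove that. There is a reason to think that timing could differ. According to the section Access to Mammography, the recruiting clinic has no mammography equipment and is served by a mobile unit three days a year, while women screened elsewhere are not tied to those dates. If the date is not recorded with the survey, no later analysis can supply it.

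**Working it through.** **1. The protocol's own figure.** Sample Size Justification: 30 IHS and 270 non-IHS women, effect size 0.54, two-sided t-test at 0.05, stated power 80%. The noncentral t-distribution with 298 degrees of freedom gives 79.9%; the normal approximation gives 80.1%. The figure reproduces, so the sample-size arithmetic is not at issue.

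**2. Share of eligible women beyond 12 months.** Inputs from the Background: 37% of eligible American Indian/Alaskan Native women report a mammogram within one year and 52% within two. Let P5 be the percentage screened within five years. The documents do not give P5, so it is varied. Among women who meet the five-year criterion:

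share beyond 12 months = (P5 − 37) / P5

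This rises with P5, and P5 cannot be below the two-year figure of 52.

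| P5 (%) | Calculation | Beyond 12 months |
|---|---|---|
| 52 (floor) | 15/52 | 29% |
| 60 (assumed) | 23/60 | 38% |
| 70 (assumed) | 33/70 | 47% |
| 80 (assumed) | 43/80 | 54% |
| 100 (ceiling) | 63/100 | 63% |

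The criticised study had 16%. The floor is 29/16 = 1.8 times that; the 60% to 80% range gives 38/16 = 2.4 to 54/16 = 3.4 times.

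**3. What an imbalance could do to the IHS contrast (illustration only; none of these values is in the documents).** Bias in SD units = difference between groups in the share beyond 12 months × shift in score from long recall.

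- 20 points and 0.2 SD: 0.20 × 0.2 = 0.04 SD; the false-positive rate goes from 5% to 5.5%.
- 40 points and 0.5 SD: 0.40 × 0.5 = 0.20 SD; the false-positive rate goes to 18%. This bias is 0.20/0.54 = 37% of the design effect.

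**4. What a restricted analysis could show.** With 30 and 270 women, the effect detectable with 80% power is (1.960 + 0.842) × √(1/30 + 1/270) = 0.54. If a fraction f of each group remains, it becomes 0.54/√f. Taking P5 from 60 to 80:

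- Within 12 months, f = 37/60 = 0.62 to 37/80 = 0.46: about 19 to 14 IHS women, detectable effect about 0.69 to 0.79.
- Within 24 months, f = 52/60 = 0.87 to 52/80 = 0.65: about 26 to 20 IHS women, detectable effect about 0.58 to 0.67.

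**The case against.** **Table 3 belongs to the pilot.** It does stand under pilot recruitment in Study 2, and the protocol never says outright that it governs Study 3. But it is the only survey eligibility table, its title is general, its item on where the last mammogram took place matches the Aim 3 contrast, and Study 3 states no criteria of its own. Applying it to Study 3 is an inference, though the natural one.

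**The lists are not closed.** The data list is introduced as demographic information, the survey items are not yet written, recency must be asked to apply the criterion, and the covariate list is left open. A full protocol or analysis plan may say more. This stands in part. A reader might infer that the date will not be collected and that recall can never be checked; the text supports only that neither its collection nor its use is stated. Even so, the list does cover mammography history and omits the date, and a yes/no screen against five years would give no elapsed time.

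**The 12-month remark concerns another study.** Correct. It sets no limit for this one, so the five-year window breaks no rule of the protocol. With low screening rates and few IHS women, a wide window is a reasonable trade.

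**The mechanism is conjecture.** A reader might infer that IHS women will have longer recall. The documents do not support that: a unit that comes every year still permits annual screening, and only one clinic is described. Nor do they support saying that long recall weakens the validity statistics. Those all come from one sitting, and faded memory could raise the correlations through a halo effect as easily as lower them.

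**Population rates are not a sample's recency mix.** Also correct. Respondents will be volunteers from a clinic and community events, and setting a projection beside an observed 16% is not a like-for-like comparison.

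**Conclusion.** The concern holds in a limited form. The protocol names recall beyond 12 months as a bias, admits mammograms up to five years old, and states neither that the date of the rated mammogram will be recorded nor that time since it will enter any analysis. If respondents resemble the protocol's own population, at least 29% would be beyond 12 months, and 38% to 54% if 60% to 80% were screened within five years. Confounding of the IHS comparison is possible, but its direction and size are unknown; the 0.04 to 0.20 SD above rests wholly on assumed values. No conclusion is drawn about the direction of any effect on the validity statistics. The point also depends on Table 3 applying to Study 3. It should be settled before the survey is locked, because a date that was not asked for is unlikely to be recovered.

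**What to change.** 1. Add one item to the survey for the month and year of the rated (most recent) mammogram, and test it in the pilot, before the form is locked.
2. Compare IHS and non-IHS global scores in a regression that includes time since mammogram as a covariate, alongside the individual factors already planned. Show its distribution by group.
3. Report a supportive sensitivity analysis in women within 24 months and, descriptively only, in women within 12 months.
4. State that Table 3 applies to Study 3, if that is intended, and add a sentence giving the reason for the five-year window in view of the protocol's remark on recall.

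Eligibility stays at five years, so recruitment is unaffected. The cost is one question in a survey meant to be brief, one covariate and a small extra analysis. The restricted subsets will be imprecise: with perhaps 14 to 19 IHS women within 12 months, that analysis can seldom settle the matter, so the covariate carries most of the weight. The reported date is itself recalled, and month and year will be less exact for older mammograms.
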